## Discussion

There exist various classifications of barriers (and facilitators) and multiple approaches for linking interventions to barriers [29-31]. In their systematic review, Légaré and colleagues propose a conceptual framework with knowledge, attitude, and behaviour as main factors [31]. Our choice of barriers is based on a list rigorously developed in the Netherlands with a literature study in 2002, expert input, and tested in various projects in the Netherlands [20]. Our main factors for ordering the barriers are related to the innovation, the healthcare professional, the patient, and the context. The barriers presented in this study correspond very well to the barriers found most often in the Légaré review, including time pressure and lack of applicability. Looking for the barriers for each individual practice and not for the practices participating in general, we decided to have the barriers proposed scored in email contact with the GPs in two rounds.

Several studies were conducted to assess the effect of tailoring implementation. In a systematic review, the authors conclude that identifying barriers and tailoring intervention to these barriers may improve clinical practice compared to no intervention and to guideline dissemination. In their meta analysis including eight studies identified with a non-tailored intervention in the control group, they report a modest effect of tailoring [13].

All data collection will take place at the end of the project period. Within the context of the evaluation of the implementation project, it is not feasible to have data collection both at the start and at the end, but the patient registration form will have baseline data on treatment issues. This also will allow for within group analyses, giving information about the effectiveness of both implementation strategies separately. Unfortunately, this data collection, either paper based or electronically, will require additional administrative actions from the practices. Enabling data collection from the electronic medical record will be beyond the scope of this project. Considering the patient questionnaire's results, with one measurement at the end, this restricts us to intergroup analyses.

Our sample size is based on power calculation considering the PACIC outcomes. In previous research, a difference of 0.5 was found in the evaluation of a CHF and a diabetes programme [32,33]. Thus, an effect size of 0.3 on PACIC can be considered a modest effect. We aim at a lowered effect because we compare two strategies that are both to be expected to have some impact.

Drug prescription is also a primary outcome measure. We will present the GAI as a measure for the percentage of indicated drugs prescribed. In previous research, many patients appeared to receive suboptimal dosages. When considering ACE inhibitors and beta blockers, we will report on the percentage of prescriptions in the indicated, high-target dosages [34].

We decided to stratify practices included based on practice size. There is some evidence of a relation between practice size and quality of care [35,37]. In one study, larger practice size was associated with more structured care [35]. Stratification of practices based on practice size could be defined as the number of GPs in the practice and based on patient list size. We choose a stratification scheme based on the former, with the strata solo, duo, and group practices, which appeared feasible in previous research leading to strata of comparable size.

CHF patients do not form a homogeneous group; apart from aetiology, we make a distinction between systolic CHF and CHF with preserved left ventricular function (diastolic CHF). In our study, both patient groups may be included, as the practice guideline gives recommendations for both the patients with and without left ventricular systolic dysfunction. Subgroup analyses will be performed.

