## Background

Chronic heart failure (CHF) is a highly prevalent chronic disease with high morbidity and mortality rates. The prevalence of CHF in the Western world is 1% to 2% in the general population and at least 10% among the age group of 85 years and older [1,2]. Mortality in CHF patients is high compared to their age group [2,3]. High morbidity is associated with high hospital admission rates and reduced quality of life [4]. There are effective, evidence-based treatments which improve mortality and morbidity but use of and adherence of treatments is suboptimal despite clinical guidelines [5-9].

A large group of patients with CHF receive treatment in primary care. There are many programmes for the management of long-term conditions in primary care -- *e.g*., diabetes, COPD and depression -- but at present not for CHF, though several disease management programmes exist for CHF related to outpatient clinics. As a substantial proportion of CHF patients do not attend such clinics but visit their GP instead, these patients are not enrolled in a structured care programme.

To improve the management of CHF in primary care, we have developed an implementation programme, comprising both educational and organisational components, the latter aimed at improved and structured care. We pilot tested this programme in 19 general practices [10]. The pilot programme was targeted at implementing the prevailing practice guideline for general practice [11]. In the mean time, in the Netherlands an interdisciplinary guideline on CHF, based on the European Society of Cardiology (ESC) guideline, was developed and published in May 2010 [12]. So, we adapted the implementation programme according to this new guideline, taking into account the lessons learned in the pilot study.

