### Objectives

The objective of the study is to examine the effectiveness of identifying barriers to change, and tailoring education and support in comparison with a standard intervention programme, to improve the management of patients with CHFin primary care.

Our null hypothesis is that tailoring does not result in better implementation of the guidelines for CHF compared to a standardised delivery of our implementation programme. In addition, we will also examine whether either of the two programmes are associated with improvements in healthcare delivery and patient outcomes.

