### Outcomes

The primary outcome measures are determined at the patients' level and consist of experience of receiving structured primary care for CHF (PACIC) and health-related utilities (EQ-5D), and of drug prescriptions.

PACIC is a questionnaire consisting of 27 items, which is related to the Chronic Care Model [24]. We translated and validated PACIC for use in general practice in the Netherlands [25]. EQ-5D consists of five questions and a Visual Analogue Scale (VAS), which has been validated for use in the Netherlands [26]. These outcome measures reflect key aspects of medical treatment, organization of care, and patient reported quality of life, and were chosen pragmatically because of the availability of relevant, validated, responsive, composite measures.

Drug prescription scores are assessed using the guideline adherence index (GAI), indicating the proportion of indicated drugs that is prescribed [27,28]. These include ACE inhibitors and beta blockers, and -- depending on the patient's CHF severity according to the NYHA classes -- further drug classes [12].

Secondary outcome measures at the patients' level concern lifestyle advice and medication during the study period, based on the patient registration forms providing information on non-pharmaceutical advice and drug prescriptions, continuity of care, and medication adherence. Considering drug therapy we will assess the percentages of ACE inhibitors and beta blockers prescribed in the evidence-based target dosages. Secondary outcome measures at the practice level are goal attainment and qualitative assessment of the programme, focussing on the subjective GP's experiences, for instance on improvement of practice organisation and collaboration with other primary care professionals.

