### Data analysis

The primary analysis is a comparison of primary outcomes at follow-up between the study groups, taking into account clustering of patients within practices. Multilevel regression analyses will be used to explore the effect of practice size and type of intervention programme. In addition, we will examine both changes within groups and differences at follow-up between groups with respect to percentage of patients on the maximum tolerated dosage of ACE inhibitor or angiotensin II receptor blocker and of beta blockage; medication completely according to the guideline; having received influenza vaccination in the winter season 2010-2011; having received professionally guided physical activity training; and the number of non-pharmaceutical issues addressed. If possible, subgroup analyses will comprise type of CHF (systolic or diastolic) and diagnostic certainty (secondary care diagnosis, echocardiography diagnosis) The interviews will be used to assess the feasibility of the programme and goal attainment, organisational changes in CHF care, and formalised cooperation with other primary care disciplines and specialist care.

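### Before-after change within an arm cannot show the effectiveness of each programme, and the per-programme objective names patient outcomes that are measured only once

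*Protocol article*

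**What the plan says.** The Objectives section first states a null hypothesis about tailored against standardised delivery. It then adds a second aim: "we will also examine whether either of the two programmes are associated with improvements in healthcare delivery and patient outcomes". For a list of prescribing and lifestyle items, the Data analysis section says "we will examine both changes within groups and differences at follow-up between groups". The Discussion gives the reading intended for the within-group part: "This also will allow for within group analyses, giving information about the effectiveness of both implementation strategies separately".

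On what can be measured, the Outcomes section gives the primary outcomes as "experience of receiving structured primary care for CHF (PACIC) and health-related utilities (EQ-5D), and of drug prescriptions". The Measures and Discussion sections give a baseline only for treatment items on the registration form. The Time frame section has the patient questionnaires sent after the project year, and the Discussion accepts the consequence: "Considering the patient questionnaire's results, with one measurement at the end, this restricts us to intergroup analyses".

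On context, the Background describes a Dutch interdisciplinary guideline, "based on the European Society of Cardiology (ESC) guideline, was developed and published in May 2010". According to the Time frame section, practices enter from June to October 2010 and newly diagnosed patients may join during the year. The Discussion says of the arms that "we compare two strategies that are both to be expected to have some impact".

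**The concern.** Randomisation here protects one contrast, tailored against standardised delivery. It does not protect a statement about either programme alone, because no arm shows what the year would have brought without a programme. The article itself supplies two other sources of change. The guideline that the prescribing outcomes track appeared just before practices entered. Patients diagnosed during the year have baseline treatment recorded at inclusion, when it may only be starting.

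There is also a mismatch between objective and data: improvement in patient outcomes under either programme needs at least two measurements, and the questionnaires provide one.

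At stake is a secondary conclusion that each programme works, drawn from changes that might have happened anyway.

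**Working it through.** **1. The plan's own figure.** Inputs from the Sample size section: difference 0.3, SD 1.0, alpha 0.05 (two-sided reproduces), power 0.80, ICC 0.05.

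- Per arm before clustering: 2 × ((1.960 + 0.842) / 0.3)² = 174.4, rounded up to 175.
- Design effect 1 + (m − 1) × 0.05: 1.35 for 8 patients per practice, 1.45 for 10.
- Total practices: 2 × 174.4 × 1.35 / 8 = 58.9 and 2 × 174.4 × 1.45 / 10 = 50.6.

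The stated 59 and 51 reproduce. They size the between-arm PACIC comparison only and say nothing about within-arm change.

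**2. What can be computed within an arm.**

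| Outcome | Baseline stated | Within-arm change |
|---|---|---|
| PACIC | No | Not computable |
| EQ-5D | No | Not computable |
| Prescribing items, GAI | Treatment at inclusion | Computable, but not attributable to the programme |
| Influenza vaccination, winter 2010-2011 | One season named, no earlier value stated | Not computable unless an earlier value is recorded |
| Number of non-pharmaceutical issues addressed | No earlier value stated | Not computable unless an earlier value is recorded |

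**3. How often background drift alone would look like an effect.** This is an illustration. The documents give no drift, no switching rate and no ICC for change in prescribing. Assumptions:

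- 60 practices split equally, so 30 per arm, with 9 patients each (the middle of the expected eight to ten): 270 patients.
- The PACIC ICC of 0.05 borrowed for the change: design effect 1.40, effective n = 270 / 1.40 = 193.
- 14% of patients switch status in either direction. A net rise d of 10 points then means 12% gain and 2% lose; 5 points means 9.5% and 4.5%; 3 points means 8.5% and 5.5%.
- No programme effect, and a two-sided 5% test.

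SE = √((0.14 − d²) / 193), z = d / SE, and the probability of significance is about Φ(z − 1.96).

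| Drift d | SE | z | One arm significant | Both arms (p²) | Exactly one arm (2p(1 − p)) |
|---|---|---|---|---|---|
| 3 points | 0.0269 | 1.12 | 20% | 4% | 32% |
| 5 points | 0.0267 | 1.87 | 46% | 22% | 50% |
| 10 points | 0.0260 | 3.85 | 97% | 94% | 6% |

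The last two columns treat the arms as independent. Using 8 or 10 patients per practice (effective n = 240 / 1.35 = 178 or 300 / 1.45 = 207) moves the one-arm figures to 19–21%, 44–49% and 96–98%.

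**4. The same question on a continuous scale.** With 30 practices per arm, 8 to 10 patients each, ICC 0.05 and an assumed before-after correlation ρ of 0.3 to 0.7, SE = √(2(1 − ρ) / effective n) in SD units. A drift of 0.1 SD is significant within an arm in 20% to 46% of trials, and 0.2 SD in 62% to 96%.

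**5. The between-arm comparison.** A drift d shared by both arms cancels: (tailored effect + d) − (standardised effect + d) leaves the difference in effects.

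**The case against.** The wording is cautious. The Objectives speak of association, and the Discussion of providing information. Within-group changes are additional to a primary analysis that is the randomised comparison. The questionnaire limit is disclosed. Before-after change in registered treatment can be reported, so the healthcare-delivery half of the second objective is not empty. Because the programme was adapted to the 2010 guideline, guideline uptake is partly what it delivers and not wholly a rival explanation. All of this stands, and it confines the point to a secondary claim. It does not rescue the word effectiveness, since the programme's share of uptake cannot be told from the rest. Nor does it remove patient outcomes from the objective.

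A reader might infer three stronger things that the document does not support:

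- **That the trial would very likely declare both programmes effective whatever the truth.** This needs a large drift. The chance that both arms are significant runs from 4% to 94% over the drifts shown, and the document gives no basis for choosing among them.
- **That one arm's significant change will be set against the other's non-significant one.** No within-arm test is stated, and the same Data analysis sentence already plans the direct between-group comparison.
- **That newly diagnosed patients will certainly inflate the change.** They may be included, but their number is not stated.

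On vaccination and issues addressed, the full form may record an earlier value, so that part is conditional.

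**Conclusion.** The point holds as a limit on what the second objective can conclude. Within-arm change in registered treatment can be described but not attributed to a programme. Within-arm improvement in PACIC and EQ-5D, two of the three primary outcomes, cannot be estimated at all, and the Objectives and Discussion do not agree on this. The primary between-arm comparison and its sample size are not affected.

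The chance that drift alone looks like an effect in one arm is about 20%, 46% or 97% for a 3-, 5- or 10-point drift. These figures rest on the assumed effective n of 193 and 14% switching. They show sensitivity to drift and are not a forecast.

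**What to change.** In the Protocol article:

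- **Objectives:** limit the per-programme aim to describing change in registered treatment items. Remove PACIC and EQ-5D from it and keep both in the between-arm comparison.
- **Data analysis:** label within-group changes as descriptive. Base conclusions on the between-arm difference, adjusted for baseline treatment where the registration form records it (prescribing items, GAI). For PACIC and EQ-5D no baseline adjustment is possible. Compare 2010-2011 vaccination and the number of issues addressed between arms only, unless an earlier value is recorded.
- **Discussion:** do not call within-group change effectiveness. State that it cannot be separated from general uptake of the May 2010 guideline or from treatment being started in newly diagnosed patients.

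Cost: mostly wording, plus a baseline covariate in the prescribing models using data the form already collects. No extra patients or measurements are needed. The sponsor gives up a claim about each programme on its own.

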The paper template is used to direct care and collect data to demonstrate the effectiveness of the interventions. Demographic data is collected in particular the aetiology of the CHF and the diagnostic category, whether diagnosis was echocardiography based, on the existence of diastolic or systolic CHF, and pharmaceutical treatment at the start of the project period. A second page poses questions about non-pharmaceutical issues such as advice about physical activity and influenza vaccination. Finally, we offer different forms for patients with systolic or diastolic CHF, based on the recommendations on medication as summarised in Table 1.

The pilot study demonstrated that three practice visits was the optimum number and these shall be offered to all participating practices. The practice visitor is an educational facilitator trained in supporting behaviour change in practices.

The pilot study also demonstrated that there was little multidisciplinary clinical activity in the improvement of care for CHF patients, and this has been addressed in this project. We now use the multidisciplinary practice guideline as a starting point instead of the monodisciplinary GP's practice guideline. Furthermore, the regional advisors will determine the social network in the practice area, providing information on other primary care disciplines, *e.g*., dieticians and physiotherapists, with extra expertise and interest in CHF treatment. These workers in the other disciplines will be informed about the project and receive relevant information in line with the multidisciplinary guideline.

All materials are offered paper based in a binder. We will also present all materials on a website and examine the possibilities for designing the guiding patient registration forms on this website as well.

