### Sample size

Power calculations are based on the primary outcome measurement PACIC. The PACIC comprises 27 questions with an answering scale from 1 to 5. A previous unreported study showed that its standard deviation was 1.0. To detect a difference of 0.3 points with a standard deviation of 1 (a relatively small effect), with alpha = 0.05 and beta = 0.20, ICC = 0.05, a total of 51 practices with 10 patients each would be required, or 59 practices with 8 patients.

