### Time frame

Practice inclusion is planned from June until October 2010. After inclusion, practices participate in the programme during one year. At the start of the year, the GPs include all their patients with CHF they treat at least in part themselves. During that year, patients with newly diagnosed CHF can also be included. Data management in the patient registration forms is a continuous process during the project year. After the project period of a year, the forms are anonymised and sent to the researchers coded. Furthermore, practices will send coded patient questionnaires with explanation of the survey and ask for an informed consent; these will be returned to the researchers. Finally the researchers will contact the GPs participating for the telephone interview. The GPs will receive feedback based on the patient registration forms and the questionnaires.

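### PACIC and EQ-5D have no baseline, and the stated model names no patient covariate, although the registration form records several and patients are included after the practice knows its arm

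*Protocol article*

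**What the plan says.** The main analysis is given under Data analysis: "The primary analysis is a comparison of primary outcomes at follow-up between the study groups", with clustering of patients in practices taken into account. The multilevel regression there has two named terms, practice size and programme type. CHF type and diagnostic certainty appear only as possible subgroup analyses.

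The Discussion explains that collecting questionnaires at both start and end was not feasible, and says of the questionnaire that "with one measurement at the end, this restricts us to intergroup analyses".

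The registration form holds patient information. Under Standardised delivery of the implementation programme: "Demographic data is collected in particular the aetiology of the CHF and the diagnostic category". That passage also lists systolic or diastolic CHF and drug treatment at the start. NYHA class is not in that list. It appears under Outcomes, where the guideline adherence index depends on "CHF severity according to the NYHA classes" for some drug classes.

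On timing, the Randomisation section has practices assigned on inclusion and then informed, with the intervention open to all. The Time frame section has GPs including patients at the start of the programme year, and newly diagnosed patients during it. At the end, "the forms are anonymised and sent to the researchers coded". The questionnaires are also coded and go back to the researchers separately.

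**The concern.** Where an outcome has no baseline value, other patient characteristics recorded at inclusion are the usual partial substitute. Here they are collected but have no stated role in the PACIC and EQ-5D models.

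Two things are at stake. The first is precision: if age, sex or CHF type predicts the outcome, leaving it out widens the interval.

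The second is comparability. Randomisation is by practice, but each GP decides which patients to include, and the sequence in the article puts that decision after the arm is known. The two arms could therefore include different kinds of patients for reasons other than chance. Without a questionnaire baseline, nobody can see on PACIC or EQ-5D themselves whether the arms started level.

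**Working it through.** **Inputs from the Sample size section.** "To detect a difference of 0.3 points with a standard deviation of 1"; "alpha = 0.05 and beta = 0.20, ICC = 0.05"; result: "a total of 51 practices with 10 patients each would be required, or 59 practices with 8 patients". Allocation 1:1 is assumed from two groups and blocks of four. Two-sided alpha is assumed; a one-sided test would need only about 40 or 47 practices.

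**Reproducing the plan's figure.** Patients per arm without clustering: 2 × ((1.96 + 0.84)/0.3)² = 174.4 (unrounded normal quantiles). Design effect = 1 + (m − 1) × 0.05, which is 1.45 for m = 10 and 1.35 for m = 8. Practices = 2 × 174.4 × design effect / m:

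- m = 10: 50.6, rounded up to 51
- m = 8: 58.9, rounded up to 59

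Both match. The sample size is sound and takes no credit for covariates.

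**Adding covariates (59 × 8, SD 1).** Let R² be the share of within-practice variance that the covariates explain. No such figure is in the document, so it is assumed over a range. The variance of a practice mean is v = 0.05 + 0.95(1 − R²)/8. The standard error of the arm difference is √(4v/59), and power is Φ(0.3/SE − 1.96).

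| R² | v | SE | Power |
|---|---|---|---|
| 0 | 0.1688 | 0.1070 | 80.1% |
| 0.02 | 0.1664 | 0.1062 | 80.6% |
| 0.05 | 0.1628 | 0.1051 | 81.5% |
| 0.10 | 0.1569 | 0.1031 | 82.9% |
| 0.20 | 0.1450 | 0.0991 | 85.7% |
| 0.30 | 0.1331 | 0.0950 | 88.5% |

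The gain at R² of 0.10 to 0.30 is about 3 to 8 points. In practices, 59 × 0.1688/0.1569 − 59 ≈ 4 and 59 × 0.1688/0.1331 − 59 ≈ 16.

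If the covariates reduce between-practice variance in the same proportion, SE is multiplied by √(1 − R²). Power is then 80.9% at 0.02 and 82.1% at 0.05. Taking both versions, low R² gains about 1 to 2 points.

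**Size of chance imbalance.** Take a binary covariate split 50:50 with ICC 0.05 and 60 practices of 8 (240 patients per arm). The SE of the arm difference in its share is √(2 × 0.25 × 1.35/240) = 0.053, a 95% range of about ±10 percentage points. If the two categories differ by 0.1 to 0.5 PACIC points (assumed), the comparison moves by 0.104 × 0.1 = 0.01 to 0.104 × 0.5 = 0.05 points, against a target of 0.3. The unadjusted standard error already includes this movement.

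**Systematic imbalance.** Its size cannot be computed from the document. The argument rests on the order of events alone: assignment, notification of the practice, then inclusion of patients.

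**The case against.** The strongest reply is that this is a condensed article, that a covariate list may sit in a full protocol or analysis plan, and that nothing here forbids adjustment. That is largely fair, and it limits the point to a recommendation. But the article does state a model and names its terms, so improving that model is more than asking for an omitted detail.

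Several stronger readings are tempting, and the document does not support them:

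- **That the Discussion wrongly rules out adjustment.** The sentence contrasts within-group change with between-group comparison. A covariate-adjusted arm comparison is still between groups, so the sentence is correct.
- **That chance imbalance biases the result.** In a randomised comparison it is already in the standard error, and the type I error rate holds. The cost of chance is precision only.
- **That severity is on every form.** NYHA class is needed for the adherence index but is not listed among the form items, so its recording at inclusion is an inference.
- **That forms and questionnaires cannot be linked, so subgroup analyses of PACIC or EQ-5D are impossible.** Both are coded and pass through the same practice. The article does not say whether the codes match, which is no evidence that they differ.

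It also stands that an R² of 0.10 to 0.30 has no support in the document for PACIC, a measure of experienced care, and that the trial is powered on PACIC. Finally, the covariates would themselves be recorded unblinded after allocation.

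**Conclusion.** The point holds as a worthwhile, inexpensive improvement to the stated analysis of PACIC and EQ-5D. It exposes no arithmetic error and no contradiction, and the missing questionnaire baseline is a disclosed limitation with a feasibility reason.

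The quantifiable benefit is precision, of the size worked out above, and it depends wholly on the assumed R². For PACIC the low end may be the realistic one. For EQ-5D a larger gain is more plausible, because health utility is more likely to vary with age and type of disease; that is a judgement, not a figure from the document.

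The second benefit is partial protection against systematic case-mix differences from inclusion after allocation. Adjustment can reduce such differences on the recorded items but cannot remove those on unrecorded ones. Only patients who consent and return the questionnaire contribute to either outcome.

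**What to change.** 1. In the primary multilevel models for PACIC and EQ-5D, prespecify a small fixed set of form items as recorded at inclusion: age, sex, CHF type, and NYHA class if it is recorded at inclusion. Keep the practice-size stratum in the model.
2. Report the unadjusted comparison beside the adjusted one.
3. State that each patient's form and questionnaire carry the same code, and set this up before the forms are anonymised.
4. Give a simple advance rule for missing form items.

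The Discussion sentence on the single measurement can stay as it is.

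The cost is a few lines of analysis text and one shared code per patient; no further patients or measurements are needed. The downsides are the handling of missing items and the use of covariates recorded by staff who know the arm. The report should say plainly that adjustment lessens selection differences without eliminating them.
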